## Abstract

**Background:**

The objective of this article is to describe the design of an evaluation of the cost-effectiveness of systematic home visits by nurses to frail elderly primary care patients. Pilot objectives were: 1. To determine the feasibility of postal multidimensional frailty screening instruments; 2. to identify the need for home visits to elderly.

**Methods:**

*Main study*: The main study concerns a randomized controlled in primary care practices (PCP) with 18 months follow-up and blinded PCPs. Frail persons aged 75 years or older and living at home but neither terminally ill nor demented from 33 PCPs were eligible. Trained community nurses (1) visit patients at home and assess the care needs with the Resident Assessment Instrument-Home Care, a multidimensional computerized geriatric assessment instrument, enabling direct identification of problem areas; (2) determine the care priorities together with the patient; (3) design and execute interventions according to protocols; (4) and visit patients at least five times during a year in order to execute and monitor the care-plan. Controls receive usual care. Outcome measures are Quality of life, and Quality Adjusted Life Years; time to nursing home admission; mortality; hospital admissions; health care utilization.

*Pilot 1*: Three brief postal multidimensional screening measures to identify frail health among elderly persons were tested on percentage complete item response (selected after a literature search): 1) Vulnerable Elders Screen, 2) Strawbridge's frailty screen, and 3) COOP-WONCA charts.

*Pilot 2*: Three nurses visited elderly frail patients as identified by PCPs in a health center of 5400 patients and used an assessment protocol to identify psychosocial and medical problems. The needs and experiences of all participants were gathered by semi-structured interviews.

**Discussion:**

The design holds several unique elements such as early identification of frail persons combined with case-management by nurses.

From two pilots we learned that of three potential postal frailty measures, the COOP-WONCA charts were completed best by elderly and that preventive home visits by nurses were positively evaluated to have potential for quality of care improvement.

## Background

### Publishing the design of a study

Publishing the design and protocol of a study before results are available is important for several reasons. A published protocol allows easier comparison between what was originally intended and hypothesized and what was actually done, and it gives readers greater insight into the methodological quality of a study [1]. Furthermore, it has often been recognized that negative or adverse outcomes are less likely to be published [2]. Publishing the design of a study before its start announces the study will be undertaken, which encourages publication of the results and in any case informs researchers where they can find the data for inclusion in systematic reviews [1,1,2]. Thus, publishing a design article can prevent publication bias. In addition, publishing pilot results provides a better insight in the choices for particular instruments and interventions.

### Primary care and elderly

In the Netherlands all people are registered in a primary care practice and Primary Care Physicians (PCPs) act as gatekeepers to specialist care, whereas for example in the USA most persons are not registered in a primary care practice [3]. There are few barriers to primary care facilities in the Netherlands and in the Netherlands about 86% of older people contact their PCP yearly [4]. Older persons in primary care are, therefore, a good representation of the total older population at risk. Primary care is confronted with increasing numbers of frail elderly because of the aging of the population, and their wish to live independently for as long as possible. Frailty poses a complex problem for primary care. Up to about 20% of the elderly, defined here as those 75 years of age and over are vulnerable for further deterioration of functional abilities and quality of life accompanied by a substantial increased risk of institutionalization [5]. This implies an exploding need for care.

Primary care is insufficiently equipped for a potential explosion of care needs. GPs are often unaware of the health status and functional limitations of their elderly patients [6,7]. Several studies reported a considerable amount of undetected morbidity both among consulting and non-consulting patients [8,9]. Moreover, PCPs, as the medically responsible person, do not regard themselves suited for systematic management and long-term monitoring for chronic diseases and disabilities associated with frail health [10].

Proactive detection of care needs in elderly but still competent persons who do not explicitly seek help is at odds with the prevailing reactive paradigm in primary care. However, as perhaps many frail elderly are unaware of the types of help available, there is a need for care experiments with transmural collaboration among health professionals, which might increase the quality of (primary) care for frail persons at home.

### Earlier interventions

Systematic home visits to frail elderly by nurses can reduce mortality and nursing home admissions provided that a substantial number of home visits are paid and care plans are based on multidimensional assessments [11,12]. In addition, accumulating evidence shows that preventive home visits are mostly accompanied by a reduction of health care costs [13]. Both from patient (health gains) and societal (cost savings) perspective this is a desirable situation.

### Frailty and preventive mechanisms

Frailty is the result of reduced ability to maintain a physiological and psychosocial equilibrium, thereby increasing the risk of functional disability, temporary or permanent loss of the ability to cope, morbidity, and mortality [14-16]. Frailty is strongly associated with aging [17,18]. The potential preventive mechanisms of home visits comprise early detection of worsening health conditions and modifiable risk factors, enabling concerted actions with responsible health professionals to optimize treatment, improve life style and increase support for family caregivers to persevere informal care.

### Costs

Aging is costly. About one third of the health care expenditures in industrialized countries relate to persons 70 years or older [19]. Nursing homes, homes for the elderly and hospital beds are occupied mainly by elderly. Elderly are massive consumers of medication. Elderly consume most home care. When the number and portion of (frail) elderly increases the health care costs will explode. Among community dwelling elderly with usual care the median annual nursing home and hospital admission rate is 2.4% (range 0–40%) respectively 26% (range 5–56%). Among frail elderly median annual admission rates are 15% and 45% respectively [11,12].

### Objectives

To describe the design of an evaluation of the cost-effectiveness of systematic home visits by nurses to frail elderly primary care patients. Pilot objectives were to determine the feasibility of postal multidimensional frailty screening instruments and to identify the need for home visits to frail elderly. This article describes the background, design and pilot results.

## Methods

### Pilot 1: Selecting frail patients by postal questionnaires (Table 2)

**Table 2 T2:** First Pilot: Selecting frail patients

Background:	Measuring frailty is subject to debate and various operational definitions were proposed [15]. For our purpose we sought a valid easy administrable self-report instrument.
Objective:	To determine the feasibility of multidimensional frailty screening instruments that could be sent by mail.
Methods:	After a literature search three multidimensional screening instruments were selected and tested in one general practice among all 75+ patients: 1) VES-13, 2) Strawbridge's frailty screen, and 3) COOP-WONCA charts. Feasibility was expressed in percentage complete item response [20–22]. Our goal was to identify the worst quarter. This point of departure was based on studies by Fried and Rockwood who reported between 20–30% of 75+ people to be frail according to their measures [14,17].
Results:	Of 116 patients 85 (81%) agreed to participate and 69 actually returned the questionnaire. The complete item response on the COOP-WONCA, Strawbridge screen, and VES-13 were 87%, 60% and 56% respectively. In order to identify a quarter of persons with the worst health on the COOP-WONCA, all persons were selected who scored in the worst quartile of at least two of the six charts (overall health ≥4; physical fitness ≥5; changes in health ≥4; daily activities ≥4; Feelings ≥3; social activities ≥3). This resulted in 23 persons who were further assessed at home by the RAI-HC. 90% had at least one chronic disease, two thirds had at least one ADL limitation, 60% had depressive symptoms (CESD>16) and 30% had cognitive impairment (MMSE<24) [37].
Conclusion:	The COOP-WONCA was the most feasible screener. Our selection rule identified a frail group. The geriatric assessment identified new potentially treatable problems.

COOP-WONCA = COOP functional health assessment charts – World Organization of Family Doctors

VES-13 = Vulnerable Elders Survey-13

RAI-HC = Resident Assessment Instrument – Home Care version

MMSE = Mini Mental Screen Examination

After a literature search three multidimensional screening instruments were selected and tested in one primary care practice among all 118 75+ patients: 1) VES-13, 2) Strawbridge's frailty screen, and 3) COOP-WONCA charts [20-22]. Feasibility was expressed in percentage complete item response. Our goal was to identify the worst quarter.

### Pilot 2: Exploring the potential for quality of care improvement of preventive home visits among elderly persons (Table 3)

**Table 3 T3:** Second Pilot : Exploring the potential for quality of care improvement of preventive home visits among elderly persons.

Objective:	To identify the need and possible benefit of home visits for frail patients, PCPs and nurses.
Method:	The setting was a health center of 5400 patients with 3 PCPs and a practice nurse. Possible frailty was determined by the PCPs among their 75+ patients in the following cases: beginning dementia, active carcinoma, two or more medications for organ indication, treatments by two or more medical specialists, being 85+ and not contacted the PCP over the last three years, uncertainty regarding the ability to manage oneself, and all other persons the PCP felt it necessary to pay attention to. The nurses visited the patients and used an elaborate geriatric assessment protocol to identify psychosocial and medical problems. The nurses and the PCPs designed a care plan. The experiences of all participants were gathered by semi-structured interviews.
Results:	The participants (PCPs, nurses, patients) evaluated this approach positively. The PCPs gained better insight in medical and care situation of their elderly patients and experienced less work pressure. The nurses experienced better quality of care. The patients felt safer and more independent. The PCP also selected a number of healthy persons.
Conclusion:	Home visits by nurses were regarded by all to have potential for quality of care improvement. Point of concern was the inadequate selection of frail patients by the PCPs. Also, the assessment protocol used by the nurses provided no triggers on when actions should follow.

PCP = Primary Care Physician

The setting was a health center of 5400 patients with 3 PCPs and a practice nurse. Possible frailty was determined by the PCPs among their 75+ patients in the following cases: beginning dementia, active carcinoma, two or more medications for organ indication, treatments by two or more medical specialists, being 85+ and not contacted the PCP over the last three years, uncertainty regarding the ability to manage oneself, and all other persons the PCP felt it necessary to pay attention to. The nurses visited the patients and used an elaborate geriatric assessment protocol to identify psychosocial and medical problems. The nurses and the PCPs designed a care plan. The experiences of all participants were gathered by semi-structured interviews.

### Main study

#### Design

A randomized controlled trial in 33 primary care practices (55 primary care physicians) among frail 75+ patients at home who responded to a Health Screener, with 18 months follow-up. Frail persons living at the same address were randomized as one unit. PCPs are held blind for the group assignment. Block-randomization ensured equal numbers of intervention and usual care patients per practice. Random number tables were used by and independent person for randomization. The ethical committee of the VU medical center approved the study.

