Therefore the nurse and the patient make a hierarchy of the problems; (3) The nurses design and execute individual suited care-plans that comply with patient priorities; (4) The nurses are case-managers and offer to visit the patients at least 5 times in a year in order to execute and monitor the care-plan, to evaluate whether the care-needs have changed and adapt the care/plan when needed; (5) The nurses also meet the PCPs on a regular basis to discus the care plans and to assure that medical actions are carried out by the PCPs; (6) To assure the quality of care, the nurses receive regularly educational updates and organize monthly meetings to discuss problematic cases. Two staff members supervise them. A national Dutch guideline on home care nursing of frail elderly patients was available [25]. This guideline was used to protocolize nurse interventions whenever possible; (7) The care plan is left at the patients' house to enable other visiting health professionals to take notice of and report on the care plan.

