#### Outcomes and measurements

Table 4 provides an overview of all outcomes and measurements in the study.

**Table 4 T4:** Measurement scheme

*Health screener*	*Instrument*	*T-1*	*T0*	*T1*	*T2*
				*6 months*	*18 months*
Functional Health status	COOP-WONCA	X		X	X
ADL & IADL	GARS	X		X	X
Cognitive decline	IQCODE self report	X			
Depressive symptoms	CES-D	X		X	X
Chronic diseases	Chronic diseases list	X			X
Mobility and Falls	Questionnaire	X		X	X
Body Mass Index	Questionnaire	X			
Weight change	Questionnaire	X			
Demographics	Questionnaire	X			
Behavioral problems	Questionnaire	X			
Incontinence	Questionnaire	X		X	X

*Main Outcomes*					
a. Health related Quality of life	SF36 + EQ5D		X	X	X
b. Hospital admissions	Patient + hospital database		X	X	X
c. (Days until) Institutionalization	PCP + nursing homes				X
d. (Days until) Mortality	Relatives + PCP				X
e. Health resource utilization	Self report + PCP + hospital + pharmacy databases		X	X	X

PCP = Primary Care Physician

GARS = Groningen Activity Restriction Scale

CES-D = Center for Epidemiological Studies – Depression Scale

IQCODE = Informant Questionnaire on Cognitive Decline in the Elderly

SF36 = Short Form 36 item version

EQ5D = EuroQuality of life

X = measurement

T-1 = pre randomization health screening

T0 = Measurement immediately after randomization

T1, T2 = Follow-up measurements

Outcomes are:

1. Health related quality of life as measured with the Short Form 36 (SF-36), and Quality Adjusted Life Years by health utilities based on Euroqol (EQ-5D) [26,27];

3. (Days until) institutionalization: Hospital stay, placement in nursing home or home for the elderly are surveyed and crosschecked at institutes;

4. (Days until) mortality as checked with the PCPs;

5. Direct costs as measured by patient questionnaires with three-monthly recall periods. These self-report data are supplemented by data from the centralized regional pharmacy database (medication use), regional hospital check, and nursing home checks. In case patients are not able to fill out the forms themselves a close relative will be approached (Table 4).

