Limitations to the generalizability of our future findings are firstly the non-response to the mailed health survey. A number of persons (n = 100) responded but did not want to participate because of their good health. We remain uncertain about other non-responders being frailer and perhaps in greater need of nurse support. In future projects alternative means for health screening may be tested in older PCP patients such as contacting consulting patients. Secondly, our RAI assessment demanded a structured approach of computer skilled persons. The computer skills of the nurses were rather limited which led to extensive additional training. Some nurses had difficulties with the computerized assessments and disliked the structured format in which the assessment took place. Thirdly, we remain uncertain about the best frailty measure to identify persons that can benefit most from preventive actions. We selected the COOP-WONCA because of its broad health definition and very good feasibility. Last, whether PCPs remain blind for group assignment during he follow up remains to be seen. It is possible that the regular contacts with the nurses will reveal some of the assignments.

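### The article says primary care physicians are blinded to assignment, but its intervention makes assignment known to them for patients whose care plans are discussed

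*Protocol article*

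**What the plan says.** The Protocol article presents blinding of the primary care physicians (PCPs) as a design feature in two places. The Methods part of the abstract describes a trial with "18 months follow-up and blinded PCPs". The Design section of the main study states that "PCPs are held blind for the group assignment". Neither is limited to the time of allocation.

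The Intervention(s) section lists seven elements, and the trained nurses contact only frail persons randomized to the intervention. Element 5, under which it is the PCPs who act, reads: "The nurses also meet the PCPs on a regular basis to discus the care plans and to assure that medical actions are carried out". Element 7, under which those professionals may also add their own reports, reads: "The care plan is left at the patients' house to enable other visiting health professionals to take notice of".

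Table 4 (Outcomes and measurements) names the PCP as one of the sources for institutionalization, mortality and health resource utilization. The Discussion closes its limitations by saying that lasting PCP blinding is uncertain: "It is possible that the regular contacts with the nurses will reveal some of the assignments".

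**The concern.** A physician cannot discuss a patient's trial care plan, or carry out a medical action arising from it, without knowing who the patient is. Having such a plan identifies the intervention arm. Delivering the intervention as described therefore removes the blinding that the abstract and Design section claim.

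This matters because the PCP has two roles. The Background describes PCPs as gatekeepers to specialist care, so their decisions feed into referrals, admissions and cost, and they also help to report several main outcomes. Someone rating risk of bias from the abstract or the Design section would credit the trial with a safeguard that its own intervention removes for the patients discussed.

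**Working it through.** The article attaches no figure to blinding, so the check is a comparison of sections plus one count.

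**1. Is the blinding claim limited to allocation?** No. The abstract couples it to the 18-month follow-up, and the Design section states it in general terms.

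**2. Does a care plan identify the arm?** Yes. Only intervention patients are contacted by the nurses, and the care plans come from those contacts. Controls receive usual care.

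**3. Is disclosure scheduled or incidental?** Scheduled. Element 5 makes regular discussion of the plans, and PCP action on them, part of the intervention. Element 7 adds a second route, since a visiting professional can read the plan at the home.

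**4. How many patients can this reach?** The Recruitment section gives 658 randomized. The Design section gives 55 PCPs, with block randomization to equal numbers per practice.
- Intervention patients: 658 / 2 = 329.
- Average per PCP: 329 / 55 ≈ 6.

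The 329 is an upper limit, because the text refers to the care plans in general and does not say that every plan is discussed. At about six per PCP, the discussions concern identifiable individuals.

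**5. Are controls revealed?** Not directly. The questionnaire went to 4823 patients, 2949 responded and 658 were randomized. A patient without a plan may be a control, a non-responder, or a responder who was not randomized.

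**6. Which outcomes does the PCP report?** Sources in Table 4 and the text below it:

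| Outcome | Sources | Role of the PCP |
|---|---|---|
| Hospital admissions | Patient and hospital database | Not a source; may influence through referral |
| Institutionalization | PCP and nursing homes, cross-checked at institutes | One source, with an independent check |
| Mortality | Relatives and PCP | One source; objective event |
| Resource utilization | Self report, PCP, hospital and pharmacy databases | One of several sources |

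The Economic evaluation adds that GP contacts and referrals are checked in the GPs' own patient files.

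**7. What follows?** The most plausible route to a difference is through care: a PCP who knows that a patient has a nurse and a plan may change contacts, referrals or admissions. Non-blind reporting comes second, through the PCP's input to institutionalization and resource use. Reporting of deaths, and of placements checked at the institutes, leaves little room for bias.

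**The case against.** The strongest reply is that the article discloses the problem. The Discussion doubts that PCPs will stay blind and names nurse contacts as the reason. Disclosure helps, but it does not resolve the contradiction. It treats as possible, and for some patients, what element 5 builds in for every plan discussed, and it leaves the statements in the abstract and Design section unqualified.

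A second reply is that PCP action on a care plan is part of the intervention and so is not a bias in the effect of the whole package. That stands, and it is why PCP contacts and referrals should be interpreted as part of the intervention effect. It does not support calling the PCPs blinded.

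A third reply is that independent sources already protect the main outcomes. Much of this stands too. A reader might infer that protection from bias is wholly absent, or that the PCPs alone supply the mortality and institutionalization data. The documents support neither: relatives also report deaths, nursing homes report placements, institutes cross-check stays, and controls are not directly disclosed.

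A reader might also try to size the bias by applying an assumed 5% relative reporting error to the 45% annual hospital admission rate quoted in the Background (0.45 × 0.05 = 0.0225, about 2 points). That figure should not be used. The 5% has no source in the article, and Table 4 takes hospital admissions from patients and the hospital database.

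**Conclusion.** The point holds in a limited form. As written, the abstract and Design section claim a property that the Intervention(s) section removes for intervention patients whose plans are discussed: at most about 329, or about six per PCP, assuming an equal split of the 658 randomized. The conclusion rests on reading a care-plan discussion as identifying the patient, which follows from PCPs having to act on the plan.

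The consequence is a changed statement about bias: PCP care of intervention patients is given with knowledge of assignment, and PCP input to institutionalization and resource use is not blind. No numerical bias can be derived from the documents. The point deserves correction because the blinding label bears on how the admission, placement and cost results will be read.

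**What to change.** - **Blinding statement.** In the abstract and Design section, replace the claim with a statement that PCPs were not told the allocation at randomization but become aware of it for intervention patients through the care-plan discussions. Reword the Discussion so that it agrees with intervention elements 5 and 7.
- **Source of events.** State that the hospital and nursing-home records already being collected determine admission and placement events and their dates in both arms, extracted without reference to allocation, with PCP report used only as a pointer to events to look up.
- **Interpretation.** State that PCP contacts and referrals are part of the intervention effect, and that PCP-supplied resource-use data are not blinded.

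The cost is rewording and a stated order among existing sources, with no new data source. The trial gives up a favourable design label.
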